**TUFTS MEDICAL CENTER/TUFTS UNIVERSITY RESEARCH PROTOCOL**

**Version date: 7/21/2017**

**Principal Investigators:** [name] [name] (IRB-PI) and [name]

**Co-Investigator:** [name]

**Study Physician:** [name]

**Study Title:** Worksite Wellness Study

1. **Aim and Hypotheses**

Worksites offer attractive locations for reducing the national prevalence of overweight and obesity. Interventions that are both effective and sustainable in producing long-term changes in health and employee wellness are urgently needed. In an 18-month worksite randomized controlled trial in 12 worksites (defined as whole, moderate sized, worksites or subunits of larger worksites) we propose the testing of two lifestyle approaches that are aimed at behavior modification for achieving long-term improvements in health and quality of life. Worksites randomized to the immediate intervention arm will receive the two wellness programs, and the randomized control sites will participate in outcomes assessments only for the initial 6 month period after which participants will be able to participate in the program of their choice. The multiple-program intervention will be tested against the control in a variety of employment types to determine effectiveness for quality of life, health and weight-related wellness across a broad range of demographics. The study will be officially registered as a clinical trial with the intention of submission to a top medical journal, and will be referred to as the Worksite Wellness Study.

The primary focus of the Worksite Wellness Study is to improve health related quality of life, with a particular focus on a decrease in cardiometabolic risk factors, improved weight-related wellness, and improved energy in work and life.

We plan to test our central hypothesis and accomplish the study objective with the following technical objectives:

1. **Conduct a randomized controlled trial assigning worksites in a 2:1 ratio to a multiple-program health intervention or a wait-listed control.** The multiple-program intervention will be a combination of the Human Performance Institute (HPI) intervention and iDiet, a behavioral weight loss program, with randomization to either partial provided food or a gift card for self-selection of food. Within worksites, employees will be eligible to select either the HPI intervention or the behavioral intervention. **Primary outcomes will be quality of life and energy levels (HPI participants and controls) and weight (weight loss intervention participants) at 6-18 months.** Secondary outcomes include cardiometabolic risk factors.
2. *The HPI working hypothesis* is that enrollment in the HPI intervention will result in significant improvements in quality of life (primary outcome) and energy levels compared to controls over 6 months and no significant decrease in quality of life during the subsequent 12-month period in the intervention participants. Exploratory outcomes also tested will include body weight and fat, fasting blood glucose, a lipid panel and systolic and diastolic blood pressure.
3. *The behavioral weight loss program working hypothesis is that* iDiet participants receiving gift card will lose weight over the first 6 months compared to weight listed controls and will lose weight compared to baseline over 18 months. In addition, iDiet participants receiving the ready-prepared foods will lose more weight over 18 months compared to participants receiving gift cards.
4. An exploratory hypothesis is that greater weight loss will be associated with reduced levels of hunger and food cravings and increased satiety.
5. **Background and Rationale**
   1. Background

Currently, one hundred and forty million people aged 20 and older are employed in the United States (1). A variety of health risks ranging from stress and lack of emotional fulfillment to obesity and physical inactivity have been correlated with a reduction in work productivity (presenteeism) (1-3). Not only do these health risks increase presenteeism in the workplace, they also increase health care costs, absenteeism, workplace injury and worker’s compensation claims (1, 3-5). Furthermore, of those currently employed in the United States, 29% of them are obese (1). Stress at work, job insecurity, lack of social support and social eating have been cited as significant contributors to this obesogenic work environment, which is on track to increase to 50% by 2030 (6-10). In an analysis of the National Health and Nutrition Surveys and the National Health Interview Survey, obese workers had the highest prevalence of weight- related diseases compared to normal weight workers, and the rate of metabolic syndrome among obese workers was 53.6% compared to 5.7% among those with normal weight. The metabolic disorders precipitated by excess body fatness are also widespread (11) and, in particular, obesity significantly increases the risk of developing cardiovascular disease, type 2 diabetes mellitus, some cancers and various skeletal disorders such as osteoarthritis (1,11,12).

As expected, there are substantial health care and other costs associated with reduced employee wellness (13). Thompson et al. (14) reported that increased expenditure of worksites for excess medical payments associated with obesity in the U.S. are $7.7 billion, costs for additional sick leave are $2.4 billion, and extra life insurance payments and disability payments are $2.6 billion. Tucker et al. (15) estimated that current health care costs for working obese individuals are over $1,000/year, which is greater than for non-obese working individuals, even ignoring the greater potential for future co- morbidities. Treatment of obesity and ongoing prevention of weight regain in worksites, if effective, holds the potential of being cost-effective when reductions in productivity and increased health care expenses for an overweight population are taken into account.

Since the worksite is an environment where people spend considerable amounts of time on a regular basis, they have been identified as an ideal forum to facilitate healthier lifestyle behaviors (16-25). Employees working together may have a positive influence on each other’s behaviors (18, 26), and from an ecological perspective, behaviors adopted by individual employees may also impact their families and communities (27). Some examples of previous worksite interventions that were successful either in making environmental changes or improving health behaviors include the Seattle 5 a Day program (28) to increase fruit and vegetable consumption; Take Heart II (29-30) to reduce smoking, decrease fat and increase fiber intake, the Next Step Trial (31) to decrease dietary fat and improve fiber consumption among auto workers through nutrition classes; the Working Well Trial (32) that improved the nutrition environments; the Working Healthy Project (33) that improved diet and physical activity behaviors and the Health and Promotion Program (23) to decrease health risks and rates of absenteeism. Additionally, research has shown that the provided foods may modify the environment presumed to influence eating behaviors, and therefore may be a useful strategy for promoting and enhancing weight-loss (34, 35).

The proposed research will implement a randomized controlled trial of two very different worksite wellness programs aimed at promoting wellness and health related quality of life, one with a particular focus on improvements in reported energy levels and the other focused on weight control. The project brings together our expertise in worksite nutrition studies, community weight loss programs and high quality health outcomes. The programs being tested differ in emphasis, approach and delivery, of the health-related wellness they recommend, and by combining them worksites potentially can reach a broader audience than if only one program was offered. The HPI program focuses on energy management and uses the sciences of performance psychology, exercise physiology and nutrition, while the iDiet weight management program emphasizes specific dietary composition goals based on recent promising weight control research by us and others (36-40) and will include an arm with provided foods. Additionally, the study will also examine whether there is a “ripple effect” of the benefits of the interventions from the worksite participants on their co-workers. This latter novel component of our study is based on research by us and others (18, 26, 27, 36, 38) suggesting that successful weight control interventions benefit both the direct participants and the household members who live with them and/or their work colleagues. For example, in a recent study by our team, weight changes were -1.3 ± 0.7kg, respectively (p=0.03) for individuals associated with individuals participating in an intervention versus the individuals associated with wait-listed controls (36). The likely explanation for this effect is that shared meals and exercise habits lead to favorable changes in energy balance in the non-participating adults, an effect that is also anticipated in worksites and, if proven here, could provide a new approach to helping resolve the obesity epidemic in worksite personnel themselves.

The interventions that are to be used in this study are all long-term group behavioral wellness programs, and implementing them simultaneously allows for a combined evaluation of these programs for concurrent use in the workplace. The combination of the 2 programs is anticipated to be highly acceptable to worksites because they are commercially available for large scale dissemination and delivery in a group format. It is anticipated that both of these programs may be beneficial in affecting wellness..

- 1. Rationale

The rationale for these technical objectives is that there is an urgent need for sustainable worksite wellness interventions generally, and two successful programs designed to achieve worksite wellness and improvements in employee health are being tested for sustainability in this long term study. Preliminary data suggests that HPI may be particularly effective in improving overall energy, as well as general and mental health, while our prototype iDiet intervention may be particularly effective and sustainable for long-term improvements in weight. Furthermore, the provision of foods for a subset of participants in the iDiet arm may facilitate adherence and overall weight control, suggesting that provided foods offer an important adjunct to enhance effectiveness of worksite weight loss programs. By conducting a comparison of the more specific dietary composition profiles in the iDiet to the energy maintenance focus of the HPI intervention we will be evaluating current best practices for an extended period of time (18 months) at worksites. The intention is to help all employees and worksites participating in this research program and to identify the most optimal long term approach to wellness, involving dietary and exercise recommendations as well as particular food provisions necessary for sustainable health. Once the results of this study are available, the most effective long-term approach to health and wellness/weight control can then be used for scaling practical, effective programs for worksite wellness.

1. **Research Plan**
2. **Experimental design:** 18-month worksite randomized controlled trial, in which worksites are randomized to receive the multiple intervention wellness programs or the control program. Control participants will participate in outcomes assessments only for the first 6 months, after which they will enroll in the intervention of their choosing. Both arms (HPI and the iDiet) will receive direct training from the coaches who deliver these commercial programs at their respective worksite and/or via a concurrent online session, or at an alternative commutable location that is offsite in the case of the HPI program. A total of 400 participants in the worksites allocated to the intervention, with approximately 20 participants in the HPI arm and 30 in the iDiet arm per worksite is planned to ensure even balance in each of the study arms. If more than 20 individuals are interested in and eligible for the HPI arm or more than 30 are interested in and eligible for the diet arm, participants will be enrolled into the study on a first-come, first-serve basis, including a small upward or downward adjustment in the total number of employees enrolled per site to ensure that the overall targeted number of participants is achieved. All participating individuals, from both the intervention wellness and control programs, can opt-in to either the HPI or the iDiet weight loss program. However, if they choose to participate in the weight loss intervention they will then be randomized into one of two groups: iDiet with food provided or iDiet with a gift card,. The study flow and primary intervention groups are described below:

**
[figure not shown]
**

*^1^The number of controls reflects study design in which sign up for the intervention and distribution of the intervention sites happens before baseline to ensure equivocal disposition*.

- Group 1: Human Performance Institute (HPI) training workshop: Is comprised of a comprehensive individual development training program that focuses on the concept of energy management. The training includes sections on a conscious evaluation of one’s goals in life, tips to manage and improve personal energy to achieve goals, as well as sessions on nutrition and exercise. The primary aim of this program is to help individuals develop attitudes, habits, and behaviors that increase their levels of daily energy, life satisfaction, and overall functioning. The course is delivered over 2.5 days in a group format with 25 – 32 participants per group by 3 coaches, each of whom specializes in one of the areas described above. Online support modules and supporting educational materials will be available to participants for the remaining 12 month period.
- Group 2: Intensive iDiet group behavioral weight loss program delivered in-person at the worksite or by videoconference and with support of the program’s web platform; This intervention will be delivered by trained nutritionists and will consist of 1-hour support and education meetings of approximately 15 participants/group with weekly messages via the iDiet message board for individual support. The 1-hour meetings will be weekly for 24 weeks (the “active weight loss” period) and then reduced to approximately once a month for the remainder of the 18-month trial. Additionally, following the weekly classes online support will also be provided for the remainder of the study (“structured maintenance” period) with additional booster classes provided on an as-needed basis. The intervention involves a diet behavioral program with particular emphasis on hunger reduction and craving control for both weight loss and prevention of weight regain.
- **Yevo Foods:** Participants will be given commercial dried food products from Yevo Intl., which are designed to help with weight control and health. Of the participants selecting the iDiet, half the group will be randomized to receive Yevo foods. Participants will be supplied with these foods monthly at the worksite for the first six months (equivalent to 2 meals/day during the first 12 weeks, and 1 meal/day for the following 12 weeks). No meals will be provided after this period, however weight maintenance in participants randomized to receive the meal will be examined for over the 18 month study duration. Participants will be asked to communicate directly with research staff for questions about Yevo foods and food vouchers, not with iDiet staff.
- **Gift Cards:** The remaining half of the iDiet participants will be randomized to receive gift cards monthly for the first 6 months, for a total of $378 and will be encouraged to purchase foods at their local grocery store.

1. **Sample size and statistical analyses**

Primary randomization is at the level of the worksites using a 2 to 1 allocation in favor of intervention; 8 worksites will receive the intervention package consisting of the 3 wellness programs and 4 worksites will be randomized as wait-listed controls.

We will enroll up to 700 individuals among 12 worksites with the goal of having 600 complete baseline assessments and get randomized to their intervention. 400 will receive one of the two intervention arms at the intervention sites, while 200 participants will be in the control sites and will participate in outcome assessments only for a six month period.

Primary outcomes measured in this study will be the change in (energy levels) vitality score as measured by the SF-36 questionnaire and change in weight from baseline to 6, 12 and 18 months. Vitality will be the primary outcome in participants in the HPI arm of the study, while weight will be the primary outcome in participants in the behavioral weight loss arm of the study.

The increase in vitality score in the intervention worksites compared to controls is expected to be 9 points at both time points compared to the control. Since randomization is at the worksite level, the total variance includes both the within worksite and between worksite variance. Based on a within worksite standard deviation of 15 and 20 people per worksite and a between worksite standard deviation of at most 3.4, 12 worksites with a 2:1 worksite allocation in favor of treatment are needed to have 80% power to detect an expected increase in vitality score of 9 points.

For the participants electing to participate in the behavioral weight loss program, randomization to either with provided Yevo foods or a gift card such that one half of the participants are in one group and the other half will be assigned to the remaining arm.. Assuming worksite is a fixed variable, 8 worksites with 30 subjects each (240 total subjects) is at least 80% powered to detect a 2.4% difference in weight loss with provided food compared to gift cards assuming no diet by food interaction. If there is a significant food by diet interaction, the study will have an 80% power to detect an interaction that is a 4.5% difference in weight change with provided food for iDiet and 3% improvement in diet.

Data analyses will be performed using the latest version of SAS for Windows, currently 9.4 (Cary, NC: SAS Institute Inc.). All testing will be two-sided and results will be judged statistically significant if the observed significance level (P value) is <0.05. Data will be examined graphically and numerically for outliers and other aberrations that might lead to misleading results. Data may be transformed prior to formal analysis if necessary to fit the assumptions for the statistical model to be employed. Both studies (HPI intervention and the iDiet intervention) will be analyzed according to Intention-To-Treat principles to best reflect what happens when individuals start one of the interventions. If necessary, missing data will be estimated using multiple imputations using the MI Procedure of SAS for Windows.

For the HPI intervention in whom those randomized to intervention will be compared primarily with subjects at control sites who elected the HPI intervention prior to workplace randomization, a mixed linear model with worksite nested within the randomization to HPI intervention or control as a random factor will be use to assess the effect of the intervention on change in vitality scale score. Baseline vitality score, weight, ethnicity and gender will be included as covariates.

The diet intervention will compare those receiving the iDiet with a primary outcome of percent change in weight at 6 and 18 months. To assess the effect of diet and food delivery method, a multi-factor model with diet, food and worksite as independent variables will be used, controlling for baseline weight, gender and ethnicity. Interactions between diet and worksite, food and worksite and food and diet will be assessed and included in the final model if significant. Change in weight for the HPI intervention andchange in vitality score for those in the diet intervention will be included as secondary outcomes.

Secondary analyses will include a comparison of the 3 intervention arms (with and without provided food for the iDiet) as well as the combined effect of intervention on change in anthropometric measures including body fat, and also lipids, blood glucose levels and blood pressure using the same models described above adjusting for the appropriate baseline values. Additionally, regression models will be used to assess the effect of different adherence metrics, activity levels, appetite regulation (hunger and food cravings) and measures of wellbeing on outcome measurements both within and between intervention groups for each arm of the study. In addition, predictors of changes in cardiometabolic parameters will be examined. Prior to enrollment of subjects, a formal data analysis plan will be prepared and submitted as part of clinical trial registration.

1. **Worksite Characteristics**

A convenient sample of worksites in the Greater Boston area, consisting of worksites which have previously expressed interest, and respond to the recruitment letters will be invited to participate in the Worksite Wellness Study. The first twelve eligible worksites with a higher employee interest in worksite wellness will then be invited to enroll in the study.

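### The second half of the HPI hypothesis is met by a non-significant test of decline from 6 to 18 months, with no margin, which is not evidence that the benefit is maintained

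*Protocol*

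**What the plan says.** Under Aim and Hypotheses, the HPI working hypothesis has two parts. The first is a significant improvement over controls at 6 months. The second, for the following year, is "no significant decrease in quality of life during the subsequent 12-month period in the intervention participants". The section on sample size and statistical analyses sets one rule for every test: "All testing will be two-sided and results will be judged statistically significant if the observed significance level (P value) is <0.05".

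The only HPI power statement concerns the comparison with controls. It takes an "expected increase in vitality score of 9 points", a "within worksite standard deviation of 15 and 20 people per worksite and a between worksite standard deviation of at most 3.4", and concludes that "12 worksites with a 2:1 worksite allocation in favor of treatment are needed to have 80% power". The protocol gives no margin, confidence-interval rule, power or SD of change for months 6 to 18, and no dropout rate. Control participants are followed untreated for 6 months and then join a programme, so the later question is within-arm.

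**The concern.** Taken together, the two statements mean that the second part of the hypothesis is met whenever the 6-to-18-month test of decline gives P of 0.05 or more, or the change is upward. A non-significant result can arise because there was no decline or because the estimate was too imprecise to show one, and this criterion cannot tell the two apart. It also rewards imprecision: the fewer participants measured at 18 months, the wider the interval and the easier the criterion is to meet.

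This matters because the Rationale says that both programmes are being tested for sustainability, and this clause is the only criterion the protocol states for whether the HPI benefit lasts. Loss of a substantial part of that benefit could be described as consistent with the hypothesis.

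**Working it through.** **Inputs from the protocol**
- Planned vitality effect: 9 points.
- Within-worksite SD 15; between-worksite SD at most 3.4 (sample size section).
- Intervention sites: "8 worksites will receive the intervention package".
- HPI participants per site: "approximately 20 participants in the HPI arm and 30 in the iDiet arm per worksite", so 8 × 20 = 160.
- Two-sided alpha 0.05.

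**Step 1. The protocol's own power figure.** Comparing 8 with 4 site means:
- SE = sqrt[(3.4² + 15²/20) × (1/8 + 1/4)] = sqrt[(11.56 + 11.25) × 0.375] = 2.925.
- Noncentrality = 9/2.925 = 3.08. With 10 df, the noncentral t gives 79.2% power.

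This reproduces the stated 80%, so a site-mean t calculation is a fair way to work with these figures.

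**Step 2. Precision of the 6-to-18-month change.** Assumptions: the SD of individual change within a site is 15, and the between-site SD of change, s, lies between 0 and 3.4. The protocol gives neither value. The vitality figures stand in for quality of life, which is what the clause names. With 8 site means there are 7 df and the critical t is 2.365.
- SE = sqrt[(s² + 225/m)/8], where m is the number measured per site.
- Half-width of the 95% CI = 2.365 × SE.
- Chance of missing a true loss L = probability that a noncentral t (7 df, noncentrality L/SE) falls below 2.365.

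No dropout (m = 20):

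| s | SE | Half-width | Missed, L = 3 | L = 4.5 | L = 6 | L = 9 |
|---|---|---|---|---|---|---|
| 3.4 | 1.69 | 4.0 | 66% | 37% | 14% | 0.5% |
| 1.7 | 1.33 | 3.1 | 51% | 17% | 3% | <0.1% |
| 0 | 1.19 | 2.8 | 41% | 10% | 1% | <0.1% |

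For example, s = 3.4 gives sqrt[(11.56 + 11.25)/8] = 1.69 and 2.365 × 1.69 = 4.0. An observed loss of up to 4.0 points (4.0/9 = 44% of the planned gain) would then be non-significant.

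**Step 3. Effect of dropout.** The rates are assumed, and dropout is taken as random so that only precision is lost. Chance of missing a true 4.5-point loss:

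| Dropout (m) | s = 3.4 | s = 1.7 | s = 0 |
|---|---|---|---|
| 0% (20) | 37% | 17% | 10% |
| 20% (16) | 42% | 24% | 17% |
| 40% (12) | 49% | 35% | 29% |
| 60% (8) | 59% | 50% | 46% |

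Loss of the full 9 points at s = 3.4 and 60% dropout is missed 7% of the time.

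**Step 4. The same data under an interval rule.** Suppose maintenance is claimed only if the 95% CI excludes a decline of 4.5 points (an illustrative margin).
- If the true decline equals the margin, a claim is made 2.5% of the time at any dropout rate.
- If there is no true change and no dropout, the claim succeeds with probability 63% (s = 3.4), 83% (s = 1.7) or 90% (s = 0).
- At s = 3.4 and 60% dropout this falls from 63% to 41%, so lost precision now counts against the claim.

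**The case against.** The strongest reply is that this is a working hypothesis and not a decision rule. The Outcomes section places the HPI primary comparison at 6 months against controls, and the HPI model and power statement serve that comparison. The protocol also promises a formal analysis plan, which is not available here. A reader might infer that non-significance is to be treated as proof, or that a faded benefit would be reported as maintained. The protocol says neither. It plans vitality changes from baseline to 12 and 18 months as well as 6, so erosion would be visible whatever the 6-to-18-month P value. Nor is HPI maintenance the trial's headline aim: the stated primary focus is improving health-related quality of life.

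The size is also open to challenge. The 3.4 is an upper bound given for the 6-month comparison. Stable site differences cancel in a within-person change, so the relevant SD may be well below 3.4. Ignoring clustering altogether, a 4.5-point loss among 160 people would be missed only 3.5% of the time. At a modest 20% dropout, the s = 3.4 figure rises only from 37% to 42%.

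A reader might also infer that the lack of later controls is hidden. It is not: the wait-list design is stated openly and the clause is confined to intervention participants.

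These replies limit the size and the consequence, but they do not rescue the criterion. It is written into the protocol's hypothesis, so an analysis plan could repair it only by departing from that wording. Multiple imputation does not help either, because done properly it carries the lost information into wider standard errors.

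**Conclusion.** The point holds as a fault in the stated criterion: a non-significant within-arm test, with no margin, cannot support a statement that quality of life was maintained, and it becomes easier to meet as precision falls. That direction is the same in every scenario computed.

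The size is conditional. It rests on vitality planning figures standing in for quality of life, an SD of change of 15, and a between-site SD of change that the protocol does not give. Without dropout, the chance of missing a loss of half the planned gain is 10% to 37% as that SD runs from 0 to 3.4. The 59% figure needs both the upper-bound SD and 60% dropout. The weakness concerns partial loss of benefit, since loss of the whole gain would nearly always be detected. The 6-month primary comparison is unaffected. The clause should be changed.

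**What to change.** Replace the no-significant-decrease clause with an estimate of the 6-to-18-month change and its 95% CI, with worksite as a random factor. Claim maintenance only if the CI excludes a largest acceptable decline that the investigators fix before seeing the data. If no margin is fixed, report the change and its CI descriptively, as an uncontrolled within-arm result, and make no claim of maintenance.

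The cost is rewording the hypothesis and its analysis; no new data are needed. The drawback is that the claim becomes harder to make. For an illustrative 4.5-point margin, no true change and no dropout, power is about 63% to 90% across between-site SDs of change from 3.4 down to 0, and it falls with dropout. The choice of margin belongs to the investigators; 4.5 is used here only to show the scale.
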